### **3.5.3 drop-out/eliminate criteria**

1) Failure to administer the medication in accordance with the dosage, method and course of treatment specified in this research program.

2) Note: Cumulative discontinuation of more than two weeks in a dosing cycle is recorded as drop-out. Failure to use the medication in accordance with the provisions of the protocol resulting in the inability to conduct efficacy and/or safety evaluations;

3) Serious violation of the protocol: concurrent application of chemotherapeutic agents and/or treatment with modern Chinese medicinal preparations with anti-lung cancer indications while participating in this study.

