### **3.5.4 Termination criteria**

1) Disease progression;

2) Grade 3/4 adverse events failure to complete treatment after dose adjustment according to the trial protocol;

3) Death;

4) Occurrence of unanticipated and unacceptable adverse drug reactions;

5) Delayed dosing for >4 weeks. Serious violation of the trial protocol (including serious violation of study enrollment conditions).

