### 3.6.2 Dose adjustment and discontinuation of administration

Anlotinib was discontinued if patients developed haemoptysis. For other grade  $\geq 3$  treatment-related adverse events (TRAEs), anlotinib was reduced to 8 mg, and the dose of chemotherapy was reduced by 25.0% of the last dose. Dose modification of sintilimab was prohibited. Patients experiencing intolerable adverse events that led to a delay or discontinuation of one drug continued treatment with the remaining study drug. Treatment continued until intolerable toxicity occurred or consent was withdrawn. Those who developed progressive disease were permitted to undergo surgery or receive SOC-CRT at the investigator's discretion.

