## 2) Safety

- Incidence of treatment-related adverse events (TRAE);
- Incidence of AEs that resulted in treatment discontinuation and/or early study withdrawal;
- Incidence of SAEs and drug-related SAEs;
- Incidence of deaths;
- Discontinuation of medication for adverse event reasons;
- Changes in vital signs before and after treatment (heart rate, blood pressure, temperature, respiration);
- Changes in whole body physical examination before and after treatment;
- Abnormalities in clinical laboratory tests.

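### The drop-out/eliminate rule in 3.5.3 conflicts with the dose-adjustment and termination rules, and the protocol does not say that such patients stay in the pCR denominator

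*Protocol*

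**What the plan says.** Protocol 3.5.3 carries the double label drop-out/eliminate and has three items:

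- Item 1: "Failure to administer the medication in accordance with the dosage, method and course of treatment specified in this research program".
- Item 2 is a note: "Cumulative discontinuation of more than two weeks in a dosing cycle is recorded as drop-out". Its second sentence adds misuse of the medication "resulting in the inability to conduct efficacy and/or safety evaluations".
- Item 3 lists as a serious violation "concurrent application of chemotherapeutic agents and/or treatment with modern Chinese medicinal preparations with anti-lung cancer indications while participating in this study".

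The Program Overview repeats item 1 and the two-week note. Neither place makes an exception for toxicity.

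Two other sections deal with the same patients:

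- 3.6.2 stops anlotinib for haemoptysis and then says: "Patients experiencing intolerable adverse events that led to a delay or discontinuation of one drug continued treatment with the remaining study drug".
- 3.5.4 lists "Delayed dosing for >4 weeks" among the reasons to end treatment.

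On the endpoints, 3.2 places the pCR rate among patients who have had surgery. Section 5.1.1 defines it on resected specimens once neoadjuvant therapy is complete. The safety list in 5.1.1 includes "Incidence of AEs that resulted in treatment discontinuation and/or early study withdrawal".

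**The concern.** The first problem is classification. A patient whose dosing is interrupted for toxicity for more than two but not more than four weeks, or who loses a drug for good, can meet the drop-out note. The same patient is still below the limit in 3.5.4 and is told by 3.6.2 to carry on with the remaining drug. The study has two centres (3.4), and nothing in the text stops them from recording the same history differently.

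The second problem is what the label does to the analysis. The word eliminate, next to an efficacy endpoint worded around operated patients who completed therapy, invites removal of these patients from the pCR denominator. Patients who fall out through toxicity or under-treatment have probably had less effective therapy, so removing them would be informative. In a single-arm test against a fixed 25%, nothing offsets that bias.

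Item 3 adds a smaller defect. Platinum-doublet chemotherapy is part of the regimen (3.6.1), yet "concurrent application of chemotherapeutic agents" carries no non-study qualifier.

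**Working it through.** **Passages side by side**

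| Patient | 3.5.3 | 3.5.4 | 3.6.2 |
|---|---|---|---|
| Interruption of 3 weeks for toxicity | over two weeks: drop-out | not over 4 weeks: treatment not ended | continues the remaining drug |
| One drug stopped for good, whole 21-day cycle without it | drop-out if calendar days of one drug count | not addressed | continues the remaining drug |
| Interruption of two weeks or less | not drop-out under the note | not ended | continues |

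Section 3.5.3 does not say whether one drug or all drugs must be off, or whether calendar days or missed doses are counted. For anlotinib this matters. Only 14 dosing days are scheduled per cycle (3.6.1), so missed doses alone can never exceed two weeks.

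**Inputs**

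- From 5.3: minimum pCR 25%, expected pCR 45%, alpha 0.05, 17 patients in stage 1, continue if more than 5 have pCR, 41 needed, 45 enrolled.
- Derived, not stated: the final boundary of more than 14 pCR in 41.
- Assumed, because the protocol gives no rate: the number eliminated and their pCR rate.

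**Reproducing the plan's figure**

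The exact probability of rejection is the sum over x = 6 to 17 of b(x; 17, p) × P(Y > 14 − x), with Y ~ Bin(n − 17, p).

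- n = 41, p = 0.25: 4.98%.
- n = 41, p = 0.45: 80.3%.

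The figures 17, more than 5, and 41 are those of Simon's optimal design at one-sided alpha 0.05 and 80% power. The value of 80% printed as the type II error in 5.3 works only as power.

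**If eliminated patients leave the denominator**

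Let the true pCR rate among all enrolled be 25%.

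(a) 45 enrolled, k eliminated, none with pCR, 41 analysed. Rate among retained patients = 0.25 × 45/(45 − k).

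- k = 2: 11.25/43 = 26.2%; type I error 7.0%.
- k = 4: 11.25/41 = 27.4%; type I error 9.8%.

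(b) As (a), but the eliminated have half the pCR rate (12.5%). Rate = (11.25 − 0.125k)/(45 − k).

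- k = 4: 10.75/41 = 26.2%; type I error 7.1%.

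(c) 41 enrolled, k eliminated, none with pCR, nobody replaced, same boundary counts. Rate = 0.25 × 41/(41 − k), with n = 41 − k in the formula.

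- k = 2: 10.25/39 = 26.3%; type I error 5.3%.
- k = 4: 10.25/37 = 27.7%; type I error 5.5%.
- k = 6: 10.25/35 = 29.3%; type I error 5.6%.

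In (c) the test is barely affected, because removing non-responders does not raise the count of responders. The reported percentage still rises.

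**The case against.** **Removal from analysis is not stated.** The two-week note says how an interruption is recorded, which is a disposition status. The only wording on evaluability is conditional on being unable to evaluate. Analysis sets usually belong in the SAP, which 5.2.1 mentions and which is not available here. This stands, so the effect on pCR is conditional.

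**A reader might infer that both primary endpoints lose the failures.** For safety the documents point the other way. The Program Overview observes adverse events in all subjects. Section 4.1 requires every adverse event in the CRF from consent until the study ends. Section 5.1.1 counts events leading to discontinuation or early withdrawal, which presupposes that those patients are kept. An understated safety rate is not supported.

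**A reader might infer that item 3 excludes everyone.** Chemotherapy that the protocol itself requires cannot be a violation of the protocol. The intent is clearly non-study treatment, and there is no plausible effect on the analysis.

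**A reader might infer a larger inflation of type I error** by assuming 15% eliminated with 41 still analysed. That needs 41/0.85 = 48.2 enrolled, which is above the planned 45.

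**The conflict may be narrower than it looks.** Discontinuation within a cycle and delayed dosing may be different quantities, and dose reductions or stops made under 3.6.2 comply with item 1. This is fair, and interruptions of two weeks or less are not caught by the note. But the protocol does not draw the distinction, and the note has no exception for stops that 3.6.2 directs. The contradiction remains for longer interruptions.

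**Conclusion.** The point holds in a limited form. Sections 3.5.3, 3.5.4 and 3.6.2 can put one patient in incompatible categories; this is visible in the text and needs no assumption. Item 3 is a wording slip.

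The upward bias in pCR depends on eliminate being applied as removal from analysis. The protocol does not say this outright, but its endpoint wording in 3.2 and 5.1.1 leans that way, and no passage says the opposite. On that condition, and with the derived 14/41 boundary, the type I error is about 7.0% to 9.8% for 2 to 4 of 45 eliminated without any pCR and 41 analysed. It is about 7.1% for 4 of 45 with half the pCR rate, and 5.3% to 5.6% without replacement, against 5.0% as designed. The elimination counts are illustrative. The safety endpoint is less affected.

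**What to change.** - In 3.5.3 and the Program Overview, state that drop-out/eliminate status does not remove a treated patient from the pCR denominator or from the safety set. A treated patient without a pCR assessment counts as not having pCR. Any per-protocol analysis is supportive only.
- Limit item 3 of 3.5.3 to anti-tumour agents outside the study regimen.
- Have the investigators reconcile 3.5.3, 3.5.4, 3.6.2 and the matching rows of the Program Overview, and say which drugs and which days count towards an interruption. No threshold is proposed here.

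The cost is wording in those sections, and a reported pCR rate that may be slightly less favourable.

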### **3.5.4 Termination criteria**

1) Disease progression;

2) Grade 3/4 adverse events failure to complete treatment after dose adjustment according to the trial protocol;

3) Death;

4) Occurrence of unanticipated and unacceptable adverse drug reactions;

5) Delayed dosing for >4 weeks. Serious violation of the trial protocol (including serious violation of study enrollment conditions).

### **3.5.5 Withdrawal Criteria**

Patients can withdraw from the study at any time, without giving a reason.

Patients must withdraw from the study if any of the following events occur:

1) Patient voluntarily withdraws from the study.

2) Subject or his/her legal representative requests to withdraw from the study;

- 3) There are medical or ethical reasons affecting the continuation of the study;
- 4) The investigator determines that withdrawal from the study is necessary in the best interest of the subject;
- 5) The subject loses to follow-up;
- 6) Subject pregnancy;
- 7) Serious violation of the trial protocol (including serious violation of study enrollment criteria).

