- [12] Echocardiogram: one examination within 7 days prior to randomization, 7 days prior to surgical resection and at the end-of-treatment visit, plus additional examinations for clinically significant electrocardiographic abnormalities during the study period.
- [13] Pregnancy test: For women of childbearing potential, a serum pregnancy test is used. Performed within 7 days prior to first dose, 1 week prior to surgery, 3-6 weeks after surgery, end of treatment/withdrawal from study, and at Visit 1 of the safety follow-up period.
- [14] Imaging: including chest CT, abdominal ultrasound; PET-CT testing and cranial magnetic resonance MRI (1.5T scanning + enhancement; cranial CT may be used instead if the patient has a contraindication to magnetic resonance testing) may be performed up to 60 days prior to the first use of the study medication; bone scans will be performed only when clinically indicated, and the bone scans must have been performed within 42 days prior to the first dose of medication.
- ✓ Screening cycle, tumor assessment can be up to 4 weeks prior to first use of study drug, and imaging results obtained prior to signing informed consent can be used for screening period tumor assessment as long as they meet RECIST 1.1 requirements.
  - ✓ Full imaging evaluation was performed after the 2nd cycle of dosing and within 7 days prior to surgery for lung cancer.
  - ✓ Subjects in whom no imaging progression is observed during safety follow-up and survival follow-up should continue to have imaging evaluations at the same frequency until disease progression or initiation of other antitumor therapy.
  - ✓ In addition to disease progression confirmed by imaging, subjects who end treatment for other reasons should also be imaged as often as possible at the frequency specified in the protocol until documented confirmation of disease progression, initiation of new antitumor therapy, or death.
- [15] Lung function assessment: Normal or mild to moderate abnormal lung function ( $VC\% > 60\%$ ,  $FEV1 > 1.2L$ ,  $FEV1\% > 40\%$ ,  $DLco > 40\%$ ) to tolerate radical lung cancer surgery; assessed within 14 days prior to the first dose of drug, and once within 7 days prior to lung cancer resection.
- [16] Pathologic evaluation: pathologic diagnosis and evaluation within 90 days prior to first dose and after lung cancer resection, respectively.

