## 3.7 Duration of research

The study is expected to last 5 years, including a 12-month enrollment period. After discontinuation of treatment, each patient will be followed-up until death or withdrawal from the study.

- Planned date for 1st patient enrollment/trial start: June 10, 2021
- Planned date for the last patient enrollment: June 10, 2023
- Planned date for the last patient to be disenrolled/end of trial: October 10, 2023 (4 months after enrollment of last eligible patient)
- Expected report date: December 30, 2023

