#### **4.9 Handling steps for patient withdrawal from follow-up program**

Patients have the right to withdraw informed consent at any time and for any reason. If a patient agrees to participate in survival follow-up, they will not be considered to have withdrawn from the study. However, if they choose not to participate in survival follow-up, they will be considered withdrawn. Therefore, investigators should make every effort to regularly contact patients to assess their health status, including at least their survival status.

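### Section 3.5.5, read with 3.7, ends follow-up for four kinds of patient who may still consent to it; section 4.9 and flow chart note [20] would keep them in EFS and OS follow-up

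*Protocol*

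**What the plan says.** Section 3.5.5, repeated under Withdrawal Criteria in the Program Overview, opens its list with "Patients must withdraw from the study if any of the following events occur". The object is the study, not the study drug. Of the seven items, 1 and 2 are a request by the patient or a representative, and item 5 is loss to follow-up. The other four are:

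- item 3: "There are medical or ethical reasons affecting the continuation of the study"
- item 4: "The investigator determines that withdrawal from the study is necessary in the best interest of the subject"
- item 6: "Subject pregnancy"
- item 7: serious violation of the protocol, including of the enrolment criteria

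Section 3.7 fixes the consequence: after treatment stops, "each patient will be followed-up until death or withdrawal from the study".

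Two other places define the end of follow-up differently. Section 4.9 states: "If a patient agrees to participate in survival follow-up, they will not be considered to have withdrawn from the study". It also asks investigators to keep trying to establish at least survival status. Study Flow Chart note [20] continues survival follow-up until one of four events: death, loss to follow-up, withdrawn consent, or termination of the study by the sponsor.

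Serious violation appears in three lists: elimination (3.5.3, by example), termination (3.5.4, run on to item 5) and mandatory withdrawal (3.5.5, item 7). None says what it means for follow-up.

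**The concern.** For a patient who meets item 3, 4, 6 or 7 and is willing to be followed, the protocol gives two opposite instructions. One ends follow-up; the other continues it.

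EFS and OS are secondary endpoints (section 3.3). Section 5.1.2 censors EFS at the last valid tumour assessment and OS at the last contact. A patient taken out under 3.5.5 is therefore censored at about the time of withdrawal, and any later recurrence or death is not counted. The usual survival estimates treat a censored patient as having the same outlook as those still followed. That is doubtful when the reason for leaving is a medical problem, the investigator's concern for the patient, or a serious eligibility failure.

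The loss would also be avoidable, because the follow-up visits and scans already exist in sections 4.6 and 4.7 and note [20].

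**Working it through.** The protocol gives no figure on this point: no expected rate of study withdrawal is stated. The check is a comparison of passages, followed by simple arithmetic on size.

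**Step 1. Does follow-up continue for a patient who still agrees to it?**

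| Event in 3.5.5 | 3.5.5 with 3.7 | 4.9 with note [20] |
|---|---|---|
| Items 1, 2: patient or representative request | Ends | Ends, if consent to follow-up is what is withdrawn |
| Item 5: loss to follow-up | Ends | Ends (listed in note [20]), with contact efforts asked for in 4.9 |
| Item 3: medical or ethical reasons | Ends | Continues |
| Item 4: investigator's decision | Ends | Continues |
| Item 6: pregnancy | Ends | Continues |
| Item 7: serious violation | Ends | Continues |

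The first two rows are ordinary exits and raise no conflict beyond the order of events for item 5: the contact efforts in 4.9 should come before the status is assigned. The last four rows conflict.

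**Step 2. Is there a rule of precedence?** None was found. Section 3.5.5 is worded as mandatory, section 4.9 is worded as a definition, and neither refers to the other.

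**Step 3. What happens in the analysis?** Take a patient found after enrolment to be a serious eligibility violation, who is resected and willing to attend visits. Under 3.5.5 item 7 and 3.7, follow-up stops, EFS is censored at the last valid assessment before withdrawal, and OS at the last contact. Under 4.9 and note [20], the same patient continues on the three-monthly and later six-monthly schedule, and a recurrence or death is counted.

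**Step 4. Size.** Inputs: planned enrolment of 45 (sections 3.4 and 5.3), and the number k of affected patients, which is assumed. If k patients have unknown status at a landmark, the lowest possible event-free or survival proportion counts all of them as events and the highest counts none. The gap is k/45:

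- k = 1: 1/45 = 2.2 percentage points
- k = 2: 2/45 = 4.4 points
- k = 4: 4/45 = 8.9 points

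The value k = 4 equals the margin between the 41 patients required in section 5.3 and the 45 planned (45 − 41 = 4). The protocol does not describe that margin as an allowance for withdrawal, so it serves only as an upper illustration.

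**The case against.** The strongest reply is that section 4.9 supplies the working definition of withdrawal, so that 3.5.5 reaches only patients who also refuse follow-up. That is a sensible reading, but the protocol does not state it, and items 3, 4, 6 and 7 make withdrawal compulsory without asking whether the patient agrees to be followed.

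A second reply is that the protocol already separates stopping treatment from leaving the study. This stands. Toxicity, progression and a patient's request to stop the drug are handled in 3.5.4, 3.6.1 and 3.6.2 and are not triggers in 3.5.5. Item 4 is met only when the investigator judges leaving the study itself to be necessary. The affected group is therefore narrower than everyone who stops the drug early.

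Several stronger readings are tempting, and the text does not support them:

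- **That surgery is cancelled.** Nothing in 3.5.5 says so, and 3.6.1 and 3.6.2 allow surgery even after progression. At most it is unclear whether the pathology result is still collected as study data.
- **That safety collection ends.** The adverse event and SAE windows run to 90 days (note [17]) and 30 days (section 6.5) after the last dose. Note [18] foresees some recording after withdrawal. Pregnancy is reportable as an SAE, which is compatible with withdrawal.
- **That note [14] is contradicted.** It says "subjects who end treatment for other reasons should also be imaged as often as possible at the frequency specified in the protocol". That concerns the end of treatment, so it is in tension with 3.5.5 and no more.
- **That survival is certainly biased upward.** Pregnancy and serious violation have no stated link to prognosis, and the mix of reasons is unknown.
- **That the two centres will produce different data.** Each could follow a different passage, but this is a possibility only.

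The repeated listing of serious violation is not an error in itself, since one event can end both treatment and participation. What is missing is its consequence for follow-up.

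**Conclusion.** The inconsistency is real and limited. For items 3, 4, 6 and 7, in a patient who has not withdrawn consent to follow-up, 3.5.5 with 3.7 stops the collection of EFS and OS data, while 4.9 with note [20] continues it.

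If the first pair is followed, a small group that is not a random subset is censored early. The resulting survival estimates could be distorted, most plausibly towards optimism if medical reasons and investigator concern make up most of the cases; that condition is an assumption. The number affected cannot be derived from the protocol, so the 2.2 points per patient describes sensitivity and is not an estimate of bias. The point concerns the secondary survival endpoints. A reader might infer an effect on the pCR test as well, but the protocol does not say that withdrawn patients leave the pCR denominator. The change is worth making because it is cheap and the loss is avoidable.

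**What to change.** Reconcile the Program Overview, 3.5.5 and 3.7 with 4.9 and note [20]:

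1. State that, whatever is decided about treatment or about taking part in study procedures, patients meeting item 3, 4, 6 or 7 who have not withdrawn consent to follow-up remain in the existing EFS and OS follow-up and in the analysis.
2. State that any surgical pathology result from these patients is still collected.
3. In 3.7, tie the end of follow-up to the same events as note [20].
4. State that loss to follow-up is assigned only after the contact efforts in 4.9.
5. Reconcile serious violation across 3.5.3, 3.5.4 and 3.5.5, and say once what it means for follow-up.

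Which events should stop treatment or study procedures is a clinical matter and is left to the sponsor and investigators. The cost is a change of wording and a few more follow-up contacts; no new visits are needed.

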## **3.6 Treatment management**

### **3.6.1 Treatment plan**

Sintilimab (200mg fixed dose) iv, d1, q3w + anlotinib 10mg, po, qd1-14, q3w + platinum-doublet chemotherapy, evaluated after 3 cycles of combination therapy and discontinued for 3 weeks (21 days) followed by surgery, which was performed within 4-6 weeks (22-42 days) of the last dose. The time between each study dosing treatment was called a cycle.

A 3-week dosing and observation cycle was established for the trial. Patients who achieved effective disease control, including complete response (CR), partial response (PR), or stable disease (SD), continued treatment until surgery as per the trial protocol (Tumor Assessment Form, according to RECIST 1.1). For patients who experienced intolerable toxicity, disease progression, or requested to discontinue the drug, treatment was terminated. In cases of disease progression confirmed by imaging, the principal investigator (PI) should promptly review and understand the situation. If certain conditions are met, the patient may still be eligible for surgery with the PI's consent: the patient must be able to tolerate the surgery in terms of symptoms or quality of life, be fully informed and willing, and the surgery should be assessed by the treating physician (investigator) as potentially providing a survival benefit. If surgery is not deemed suitable, the patient may instead undergo standard radiotherapy treatment with the PI's consent.

| NSCLC                                                            |                                 |                                    |                        |
|------------------------------------------------------------------|---------------------------------|------------------------------------|------------------------|
| Drugs in the research                                            | Mode of administration          | Frequency                          | Duration of treatment* |
| Sintilimab
(200mg fixed dose)                                 | Intravenous,
over 30 minutes | Day 1
(one cycle every 3 weeks) | 9 weeks                |
| Anlotinib 10mg                                                   | Oral                            | Daily
(2 weeks on, 1 week off)  | 9 weeks                |
| Platinum-doublet
chemotherapy (guideline
recommended drug) | Intravenous                     | Day 1
(one cycle every 3 weeks) | 9 weeks                |

\*1 cycle = 3 weeks, treatment duration = 3 cycles

The medication record (Sintilimab and anlotinib) is confirmed through the following table.

A Prospective Single-arm, Open-label Study of Sintilimab and Anlotinib Combined with Chemotherapy in Neoadjuvant Treatment of Resectable NSCLC

Research Center Name/No.: The Second Affiliated Hospital of Air Force Medical University (Tangdu Hospital)/01  
Principal Investigator: [name]

